#### Blinding

Patients as well as treating physicians are blinded until 60 min after initiation of the infusion at the latest. After 60 minutes at the latest, the medication is unblinded in order to be able to decide on further treatment.

For unbiased evaluation of the primary endpoint final EEG is assessed by two expert raters (EEG reference board) blinded to treatment arm allocation.

#### Standardisation

Endpoints like infections are defined in detail in working instructions. Furthermore, standardisation of procedures will be achieved by providing an intervention package for each study patient containing a detailed plan with step by step guidance. Local study teams will be trained in personal sessions by members of the coordinating investigator team at initiation visits. Depending on demand, further training activity will be delivered as a webinar or telephone conference. All diagnostic EEGs are assessed retrospectively by a two blinded external expert raters 1) for quality assurance and 2) to determine protocol deviations leading to exclusion of the patient from the per-protocol analysis.

## 8.2 End Points

### 8.2.1 Primary End Point

Primary endpoint is the effectiveness of intravenous valproate (VPA) or levetiracetam (LEV) to terminate eSE and maintain control of epileptic activity **up to 60 minutes** after initiation of the trial intervention defined:

- ⇒ for patients with CSE: cessation of convulsions within 15 min after initiation of infusion, subsequent stable cessation of convulsions during 60 minutes after initiation of infusion.
- ⇒ for patients with NCSE: cessation of EEG signs of NCSE according to Salzburg criteria (Leitinger et al. 2016) within 15 min after initiation of infusion, subsequent stable cessation of ictal EEG activity according to the Salzburg criteria during 60 minutes after initiation of infusion as evaluated by the external EEG reference board.

Evaluation of this endpoint is possible for each patient.

Statistically, the time to cessation as well as the success rate is evaluated.

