| VPA or LEV infusion     |                | X                                   |            |            |            |                                         |                       |                |
| GCS                | X              |                                     | X          | X          | X          |                                         |                       | X              |
| Neurological exam              | X              |                                     |            |            | X          |                                         |                       | X              |
| mRS/BI             | X  |                                     |            |            |            |                                         |                       | X              |
| Home care                      | X  |                                     |            |            |            |                                         |                       | X  |
| Adverse events                 |                | X                                   |            |            |            |                                         |                       |                |
| Recurrence seizures/SE         |                | Recorded any time until discharge   |            |            |            |                                         |                       |                |
| Clinical data     |                | X                                   |            |            |            |                                         |                       |                |

Follow-up-visit, at day of discharge or day 30

by legal or authorised representative **or** according to §41 AMG (1)

cardiopulmonary monitoring

electroencephalography, only patients with NCSE

complete blood count, liver, kidney function, sodium, level of VPA, level of LEV

Glasgow Coma Scale

modified Rankin Scale/Barthel Index

premorbid state by patient (retrospective) **or** relatives

after hospital stay (if applicable)

clinical data about the hospital stay, i.e. infections with i.v. antibiotics, special medications, initiation and duration of invasive/noninvasive ventilation, recorded on day of discharge/day 30

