Though phenobarbital has been widely used for treatment of SE and its efficacy has recently been confirmed again (Brigo et al. 2019) its clinical utility is limited by the central depressive effect with sedation, respiratory depression and by hypotension which are enhanced by prior administration of benzodiazepines (Trinka et al. 2015). The efficacy of LCM has been

investigated in several studies with different designs that indicate LCM as a more promising option for focal types of SE than for refractory or nonconvulsive types of SE. Reliable prospective data about the comparison to the recommended therapies are missing (Farrokh et al. 2019). Caution is recommended in patients with cardiac comorbidities because of the possible prolongation of the PR-interval in LCM (Leitlinie, Deutsche Gesellschaft für Neurologie; Strzelczyk et al. 2017).

Beyond these two stages anesthetics are used to control SE.

To face the lack of evidence the multicenter RCT “Established Status Epilepticus Treatment Trial - ESETT” (launch in 10/2015) enrolled patients over 2 years with no upper age limit and compared VPA, LEV and fosphenytoin as the treatment for established SE. Seventy of the enrolled 384 patients were older than 60 years old. Only convulsive SE has been considered in this trial. The anticonvulsant drugs each led to seizure cessation and improvement of consciousness by 60 minutes in approximately half of the patients with similar incidences of adverse events. (Kapur et al. 2019) Also first results of a German observational study about SE-treatment in adults are published which focus on the initial termination (Kellinghaus et al. 2019). No new evidence regarding treatment of SE in elderly people can be derived from this study. Another German observational study about outcome, economical issues and quality of life after SE is still recruiting (DRKS00008718).

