### 4.1 Inclusion Criteria

Patients must meet ALL of the following criteria:

1. Diagnosis of established status epilepticus defined as:
  - ongoing convulsive seizures (generalized/focal with impairment of consciousness/ focal without impairment of consciousness) for the duration of  $\geq 5$  minutes
  - or
  - 2 or more repetitive convulsive seizures without full recovery of consciousness between the seizures for the duration of  $\geq 5$  minutes
  - or
  - ongoing EEG patterns consistent with definite or possible NCSE according to the Salzburg criteria (Leitinger et al. 2016):

EEG patterns have to be continuously present for at least 10 seconds and the whole EEG recording should be abnormal AND

- epileptiform discharges (spikes, polyspikes, sharp-waves, sharp-and-slow-wave complexes) >2.5 Hz
- or**
- epileptiform discharges  $\leq 2.5$  Hz **with**
  - fluctuation **or**
  - typical spatiotemporal evolution **or**
  - subtle clinical ictal phenomenon
- or**
- rhythmic delta/theta activity (>0.5 Hz)

() definition of fluctuation (Hirsch et al. 2012): >3 changes ( $\leq 1$  minute apart) in frequency (by at least 0.5 Hz), >3 changes in morphology, or >3 changes in location (by at least 1 standard interelectrode distance)

**or**

- clinically defined NCSE (\*)

that do not respond to the treatment with an adequate dosage of benzodiazepines. Adequate dosages are AT LEAST:

- Lorazepam 2 mg i.v.
- Midazolam 5 mg i.v./intranasal/buccal/i.m.
- Diazepam 5 mg i.v./rectal
- Clonazepam 1 mg i.v.

The dosage may exceed the minimum adequate dosage as indicated above. The antiepileptic drugs may be administered in fractionated doses.

The last administration of benzodiazepines was 5 to 30 minutes prior to start of intervention.

(\*) Clinically defined NCSE may be diagnosed in the following circumstances:

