## 6.2 Enrolment in the Trial

The inclusion of patients with convulsive SE follows the consideration of the inclusion and exclusion criteria without further diagnostic procedures. The diagnosis NCSE usually requires the confirmation by EEG.

Generally, the local investigator at the trial site may **prescreen** subjects for general participation in the current study on the basis of pre-existing data (diagnosis status epilepticus and age ≥ 65 years). All prescreened patients are listed on a pre-screening list.

**NOTE:** Procedures performed solely for the clinical study can be performed only after inclusion procedures described in chapters 4.3 and 6.1.

At first, general inclusion/exclusion criteria are checked, demographic data are recorded, blood sampling for local laboratory test and if any, further examinations are performed in order to check all inclusion and exclusion criteria - before randomisation (see 6.2.1).

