#### Randomisation procedure

Randomisation lists are created by statistical software. Blocks of randomly chosen length are created as realisations of random samples and stringed together to a list.

ZKS Leipzig delivers one randomisation list per centre each to the central pharmacy Erlangen. Beginning with the first entry in the randomisation list, the staff of the pharmacy packs medication kits for one patient each. Every kit is labelled by a consecutive ID number and contains a sealed opaque envelope revealing the information about the medication. A pre-defined number of kits are packed into a package and are sent to the trial sites. The medical personal in the trial sites is obliged to take the set with the lowest ID number. Treatment failure is defined as clinical evidence of epileptic activity and / or persistent electroencephalographical ictal activity consistent with NCSE according to the Salzburg criteria 15 minutes after the initiation of intervention or recurrence of ictal activity (in case of NCSE return of EEG patterns to baseline status after initial treatment response) during the further 45 minutes observing period which leads to immediate unblinding of medication. In case of treatment success, drug therapy will be unblinded after 60 minutes to ensure appropriate further treatment (see Figure 1). The investigator is responsible that the envelope is not opened before.

Every trial site is equipped first with a start package of fixed number of medication sets. The size of further packages may be adapted in accordance to the accrual of the trial sites.

The trial sites inform the ZKS about every included patient and transfer the medication ID. Matching the randomisation list with the correspondent list from the central pharmacy Erlangen, the ZKS is able to oversee the randomisation process and the medication logistics.

By study design most of the effects in secondary endpoints cannot be unequivocally attributed to the trial medication. Regarding the parameters, they are not susceptible to biased evaluation either. To minimize bias arising from evaluation of EEG-patterns, EEG evaluation trainings shall be performed. Each trial site will be equipped with working instructions to ensure homogeneity of procedures. These working instructions will cover:

1. The preparation of the intervention
2. The procedures during 60 minutes after the start of intervention
3. The procedure of uploading the EEG data
4. The report of AEs.

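### The repeated-seizure entry route for convulsive SE does not require convulsions at T0, yet success is scored on absence of convulsions alone and without EEG, so some patients start in the success state and silent SE counts as termination

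*Protocol*

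**What the plan says.** Section 4.1 lists two convulsive entry routes joined by a plain or. The first is convulsions ongoing for at least 5 minutes. The second is "2 or more repetitive convulsive seizures without full recovery of consciousness between the seizures", again for at least 5 minutes. All routes carry the condition of non-response to an adequate benzodiazepine dose, and 4.1 adds a time window: "The last administration of benzodiazepines was 5 to 30 minutes prior to start of intervention". The English synopsis puts both routes under the label of ongoing convulsive SE. Section 6.2 states: "The inclusion of patients with convulsive SE follows the consideration of the inclusion and exclusion criteria without further diagnostic procedures".

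Section 8.2.1 introduces the primary endpoint as ending eSE and keeping epileptic activity under control up to 60 minutes. For CSE it is made operational as "cessation of convulsions within 15 min after initiation of infusion, subsequent stable cessation of convulsions during 60 minutes after initiation of infusion". The NCSE version is read from the EEG by the external reference board. Footnote 4 of the schedule of assessments limits EEG: "electroencephalography, only patients with NCSE".

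Section 8.1.1, under the randomisation procedure, gives a separate definition of treatment failure: "clinical evidence of epileptic activity and / or persistent electroencephalographical ictal activity consistent with NCSE according to the Salzburg criteria 15 minutes" after the start of the intervention, or a later recurrence. GCS is taken at screening, T15, T30 and T60, but vigilance at 60 minutes is only a secondary endpoint (8.2.2).

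**The concern.** In the second route the patient is in SE because consciousness does not return between convulsions. That feature is absent from the exit rule. A patient who had repeated convulsions, received a benzodiazepine up to 30 minutes earlier, and lies unresponsive but not convulsing at T0 can be enrolled. This patient shows no convulsions before any drug effect is possible.

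There is a related gap for CSE patients by either route. If convulsions stop but SE continues without motor signs, the patient meets the CSE success definition, and no scheduled EEG could show otherwise. Section 1.1 itself describes NCSE as frequent in older people, hard to diagnose and mostly in need of EEG validation.

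Two things are at stake. Successes that do not depend on the drug pull the VPA-LEV difference towards zero and raise both cessation rates, although 1.2.1 wants dependable estimates for each drug. In addition, the CSE result would be reported as control of epileptic activity when only convulsions were assessed.

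**Working it through.** **Step 1: the rules side by side.**

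| Element | First CSE route | Second CSE route | NCSE |
|---|---|---|---|
| What makes it SE (4.1) | Convulsions ongoing for 5 min or more | Repeated convulsions, consciousness not regained between them | EEG pattern, or a clinical definition |
| Convulsing at T0 required | Implied by ongoing convulsions | Not stated | Not applicable |
| Success (8.2.1) | No convulsions by 15 min and to 60 min | Same | EEG signs gone by 15 min and to 60 min |
| EEG scheduled | No | No | Yes |

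For the first route, entry and exit match: both concern convulsions. For the second they do not. The benzodiazepine condition does not settle the matter, because 4.1 does not say what non-response means for someone who has had no further convulsion since the dose but has not woken up.

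**Step 2: 8.1.1 against 8.2.1.** The failure definition in 8.1.1 covers any clinical sign of epileptic activity as well as ictal EEG, and is not confined to NCSE patients. The T15 check in 6.3 also lists minimal rhythmic motor activity. A CSE patient with subtle twitching but no convulsions at 15 minutes could therefore be a failure under 8.1.1 and a success under 8.2.1. For purely electrographic SE, the broader wording has no scheduled EEG in CSE patients to act on.

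**Step 3: reproduce the plan's sample size.** Inputs from 8.3.1 and 8.4: 60% (VPA) against 47% (LEV), two-sided 5%, power 80%.

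n per arm = (1.96 + 0.8416)² × (0.60×0.40 + 0.47×0.53) / 0.13² = 227.15, total 454.3. The stated 454 is reproduced, so this point is not about an arithmetic error.

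Power at 227 per arm = Φ(0.13 / √[(0.2400 + 0.2491)/227] − 1.96) = Φ(0.84) = 80%.

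**Step 4: illustration of dilution.** Assumptions, none of them given in the protocol: a share q of all patients is not convulsing at T0; they succeed with probability s in either arm; the rest follow 60% against 47%.

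Observed rate = (1 − q)·p + q·s, so the difference is (1 − q) × 13 points. Power uses the formula of step 3.

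| q | Difference | Rates at s = 80% | Rates at s = 90% | Power |
|---|---|---|---|---|
| 0 | 13.0 points | 60.0 v 47.0% | 60.0 v 47.0% | 80% |
| 5% | 12.4 points | 61.0 v 48.7% | 61.5 v 49.2% | 76% |
| 10% | 11.7 points | 62.0 v 50.3% | 63.0 v 51.3% | 72% |
| 20% | 10.4 points | 64.0 v 53.6% | 66.0 v 55.6% | 62 to 63% |

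**Step 5: how far this depends on equal success.** Suppose VPA prevents recurrence better in these patients, say 90% against 80% (again an assumption). At q = 20% the rates are 0.8×0.60 + 0.2×0.90 = 66.0% and 0.8×0.47 + 0.2×0.80 = 53.6%. The difference is 12.4 points and power is about 78%, so most of the loss disappears.

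**The case against.** The strongest reply has four parts.

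*Eligibility.* Every route requires benzodiazepine non-response, and the synopsis calls both convulsive routes ongoing SE. One could argue that a patient with no convulsion since the dose has responded and is not eligible. That reading is possible, but the text does not impose it: the synopsis defines ongoing SE by the same second route, and non-response is left undefined for it. The objection turns a certainty into an ambiguity; it does not remove it.

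*Scope.* A reader might infer that every CSE patient with impaired consciousness is scored on something other than what defined the SE. The protocol does not support that. In the first route it is the duration of convulsions that defines SE, and impaired consciousness only names the subtype.

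*Size.* A reader might also take the figures above as a predicted loss of power. They are not. Only second-route CSE patients can contribute; if, as an assumption, half of the patients had NCSE, q = 20% would mean 0.20/0.50 = 40% of all CSE patients not convulsing at T0. A convulsion after T15 is still a failure, so the drugs can differ in these patients. The planning rates come from published studies that 8.4 says vary in design and endpoint definition, so they may already include such patients.

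*Consciousness.* Section 1.1 describes the result of the earlier three-drug randomised trial as "seizure cessation and improvement of consciousness by 60 minutes in approximately half of the patients", and it is tempting to demand the same here. The protocol never adopts that standard. A required GCS rise would be confounded by benzodiazepines and possibly by the study drug: 5.5.2 reports somnolence and sedation as the most frequent LEV effects, and depressed consciousness in 15 (LEV) against 9 (VPA) patients in that trial. This part of the objection stands in full.

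It is also fair that detailed analyses belong in the SAP and that the eCRF is not shown. The state at T0 may be captured there, but the protocol does not list it as an assessment; screening asks only for SE status and type. Eligibility, the endpoint definition and the EEG schedule, however, are fixed in the protocol.

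**Conclusion.** The point holds in a limited form. A second-route CSE patient who is not convulsing at T0 begins in the success state, and electrographic SE that persists after convulsions stop is scored as termination of eSE. Sections 8.1.1 and 8.2.1 define failure and success on different grounds, and the broader one cannot detect silent SE in CSE patients without EEG.

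The size is unknown. Under the illustrative assumptions of 5 to 20% affected and 80 to 90% success regardless of drug, the difference shrinks from 13 to between 12.4 and 10.4 points, and power from 80% to between about 76 and 62%. The loss is smaller if the drugs differ in preventing recurrence or if the planning rates already contain such patients. The documents do not support saying that the trial is underpowered by any particular amount. What is certain is narrower: for CSE, the endpoint as written measures clinical cessation of convulsions, and the claim should match it.

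**What to change.** 1. Record at T0, for every CSE patient, whether the patient is convulsing (yes/no), and list this among the T0 items in 6.3.
2. Pre-specify a sensitivity analysis of the primary endpoint that is restricted, for CSE, to patients convulsing at T0. NCSE patients stay in as planned.
3. Reconcile the failure wording in 8.1.1 with the endpoint in 8.2.1, so that each CSE patient has one unambiguous classification.
4. Word the CSE result as clinical cessation of convulsions, not as termination of epileptic activity.
5. Optionally, report a supportive analysis that also requires a better GCS at T60 than at screening. Label it as confounded by benzodiazepine and possibly LEV sedation, and do not let the conclusion depend on it.

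The cost is one eCRF field, a small extra analysis and a slightly narrower stated conclusion. No additional patients or EEG recordings are needed.

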The ESET trial (Kapur et al 2019) reports a depressed level of consciousness and respiratory distress as most frequent serious adverse events. The incidence of these events did not differ significantly between the treatment groups (LEV, VPA and fosphenytoin). Numerically depression of consciousness (15 vs. 9) and respiratory depression (10 vs. 8) was more often in the LEV treatment arm than in the VPA treatment arm (Supplement to Kapur et al. 2019).

During the intervention of ToSEE the relevant acute side-effects as hypotension and respiratory depression are recorded by the cardiopulmonary monitoring. In addition at least one member of the trial staff will guard the patient and check his clinical status repeatedly during 60 minutes after the start of the intervention. According to the clinical standard of SE-treatment rescue medication and airway-management shall be provided. The lab analysis before the intervention and after the observation period serves the detection of pre-existent and acute hepatic or renal impairment.

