#### Efficacy

- Time from initiation of trial intervention to cessation of eSE within 60 minutes
- Neurological status (including vigilance) 60 minutes after initiation of intervention

- Difference of blood levels of VPA and LEV before and 60 minutes after initiation of intervention
- Recurrence of seizures or nonconvulsive/ convulsive SE after initially successful intervention
- For patients who failed the primary endpoint, number of patients in whom SE ceased during 60 minutes after initiation of intervention according to the treating physician
- For NCSE patients who failed the primary endpoint, time to first cessation, as verified by EEG
- Number of patients with SE-associated ventilation until hospital discharge
- Functional outcome at discharge, defined by Barthel Index (BI) and modified Rankin Scale (mRS)

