#### Safety

- Mortality
- Need for any emergency medication (different from allocated study drug) during 60 minutes after initiation of study intervention
- Need for ventilation (noninvasive/ invasive) during 60 minutes after initiation of intervention
- ~~Number of patients with SE-associated ventilation until hospital discharge~~
- Intrahospital complications
  - Incidence of delirium as diagnosed by the treating physician
  - Infections requiring intravenous administration of anti-infectives
  - Adverse events related to infusion/subsequent therapy with antiepileptic drug (sedation, dizziness, nausea, vomiting, thrombocytopenia, leukopenia, hypotension, new elevation of liver enzymes, hyperammonaemia, acute new liver failure or pancreatic damage, tremor, psychiatric abnormalities)

The mRS is the recommended outcome measure in stroke trials as it is directly relevant to the patient's ability to return to daily life. Its scores range from 0 (no impairment) to 6 (death) and include special items as walking and independence that are indicative of the degree to which a patient is competent to participate in daily activities (Lees et al. 2012). As most of the seizures occurring in elder people are caused by an underlying structural brain injury the clinical phenomenology of focal convulsive SE or nonconvulsive SE may imitate stroke-related deficits. Thus, the effects on functional outcome may be quantified meaningfully and appropriately by the mRS. The Barthel Index is also a well-established clinicometric scale which is utilized to reflect elderly patient's need for care in particular and includes basic activities such as transfer and personal hygiene (Mahoney and Barthel 1965).

The secondary endpoints will provide valuable insights into the disorder in this age group. There is a special emphasis on characteristics of SE and concomitant intrahospital complications to provide an equal evaluation of the efficacy and safety of antiepileptic treatment in the elderly.

The combination and comparison of the retrospective and prospective assessment of mRS and BI are chosen in order to quantify its consequences on functional outcome.

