## **11 REFERENCE EVALUATIONS**

All study related electroencephographical data will be evaluated by a central committee consisting of two external expert reviewers (EEG reference board) who are medical specialists in neurology and also experts for epileptology. They are blinded to the treatment; clinical data of the patient will not be provided. For the purpose of the external review every trial site transfers the pseudonymized EEG data to a study specific cloud, the related server is located at the ZKS Leipzig. Access to the EEG data is restricted to the reviewers. Each trial site is only permitted to upload data. The pseudonymisation can be realized in the following manner:

- ⇒ the clinical recording of a patient will be stopped and a new record labelled with the patient ID, will be started
- ⇒ after converting the data in an edf file the heading with the patient related information can be read out in a text editor and pseudonymisation can be checked before the transfer to the cloud

Reference evaluation of the EEGs will be completed within 1 month. Disagreement between the two expert raters will be resolved by discussion. If the EEG reference board disagrees with the diagnosis NCSE in more than 25% of all cases contributed by a given trial site over a year the trial staff of that site will undergo additional training.

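### The primary endpoint has no rule for other antiseizure or sedative drugs, or for death, before 60 minutes, so a few patients could be credited to the wrong treatment

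*Protocol*

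**What the plan says.** Section 8.2.1 opens with the aim: "Primary endpoint is the effectiveness of intravenous valproate (VPA) or levetiracetam (LEV) to terminate eSE and maintain control of epileptic activity". Success is then defined by seizure type. For convulsive status (CSE) it is "cessation of convulsions within 15 min after initiation of infusion, subsequent stable cessation of convulsions during 60 minutes after initiation of infusion". For nonconvulsive status (NCSE) the EEG signs must clear within 15 minutes, with "subsequent stable cessation of ictal EEG activity according to the Salzburg criteria during 60 minutes after initiation of infusion", as judged by the external EEG reference board. The section adds: "Evaluation of this endpoint is possible for each patient".

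Section 8.1.1 (Randomisation procedure) gives the mirror image. Failure is clinical or EEG ictal activity at 15 minutes, or recurrence in the following 45 minutes.

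Other treatment in the same hour is foreseen. Section 5.5.2 says that "rescue medication and airway-management shall be provided". Section 8.2.2 lists "Need for any emergency medication (different from allocated study drug) during 60 minutes after initiation of study intervention" among the safety endpoints, beside ventilation within 60 minutes and mortality. None of these enters the primary endpoint.

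Three further provisions matter:
- Study EEG is recorded in NCSE patients only (Schedule of Assessments, footnote 4).
- Section 11 says of the board members: "They are blinded to the treatment; clinical data of the patient will not be provided".
- Section 8.2.1 says that time to cessation is evaluated too, and 8.2.2 lists "Time from initiation of trial intervention to cessation of eSE within 60 minutes".

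**The concern.** The aim concerns the effect of one drug, while the definition records only whether seizures are seen. The two separate once a second agent is given. If that agent stops the seizures, or makes a recurrence impossible to see, the allocated drug gets the credit under the literal wording. A patient who dies without further ictal activity has no stated score, although the section says the endpoint can be evaluated for everyone.

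Second agents are more likely where the allocated drug is doing badly. Crediting them would overstate both absolute success rates. If it happened to a similar extent in both arms, the difference between arms would also shrink. The rates matter in their own right: 1.2.1 and 8.7 say the full sample is wanted for reliable estimates even if no difference is shown.

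**Working it through.** **Which patients are affected.** The success rule in 8.2.1 and the failure rule in 8.1.1 can be applied to each course of events.

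| Course | Score under the text | Attributable to the allocated drug? |
|---|---|---|
| Still ictal at T15, rescued afterwards | Failure | Correctly a failure |
| Ceased by T15, recurrence observed, then rescued | Failure | Correctly a failure |
| Another agent before T15, status gone at T15 and to T60 | Success | Unclear |
| Ceased by T15, then another anticonvulsant, sedative or anaesthetic, no recurrence seen | Success | Unclear after that drug; in CSE there is no study EEG to show hidden activity |
| NCSE, local failure call, another drug given, board reads no ictal activity from T15 to T60 | 8.1.1 points to failure on clinical evidence; 8.2.1 leaves it to the board, so success | Unclear after the drug; the board cannot know of it |
| Death before T60 without ictal activity from T15 | Not stated | No |

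The first two rows are the usual rescue cases and are scored properly. Section 8.2.2 also counts primary failures whose status stops within 60 minutes as a separate secondary endpoint, so later cessation does not reverse a failure. The last four rows are the gap.

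**The plan's own figure.** Inputs from 8.3.1 and 8.4: 60% (VPA) and 47% (LEV), two-sided 5%, power 80%, 1:1 allocation.

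n per arm = (1.960 + 0.842)² × (0.60 × 0.40 + 0.47 × 0.53) / 0.13² = 227.15, so 2 × 227 = 454, as stated. With a pooled-variance test, power at 227 per arm is 79.5%.

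**Illustration of size.** The protocol gives no rate for the four rows. Assume a share m of true drug failures is scored as success in both arms:

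p(VPA) = 0.60 + 0.40m; p(LEV) = 0.47 + 0.53m; difference = 0.13 × (1 − m).

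| m | VPA | LEV | Difference (points) | Power, 227 per arm |
|---|---|---|---|---|
| 0 | 60.0% | 47.0% | 13.0 | 79.5% |
| 2% | 60.8% | 48.1% | 12.7 | 78.0% |
| 5% | 62.0% | 49.7% | 12.4 | 75.6% |
| 10% | 64.0% | 52.3% | 11.7 | 71.6% |

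In patients, m = 5% is 0.05 × 0.40 × 227 = 4.5 in the VPA arm and 0.05 × 0.53 × 227 = 6.0 in the LEV arm. At m = 10% it is 9.1 and 12.0.

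**Unequal shares.**
- Only LEV failures misclassified, m = 5%: difference 60.0 − 49.65 = 10.35 points, power 60.1%.
- Only VPA failures misclassified, m = 5%: difference 62.0 − 47.0 = 15.0 points, so the effect is inflated.
- Both true rates 53.5%, misclassification in one arm only: false rejection 7.9% at m = 5% and 16.9% at m = 10%, against a nominal 5%.

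**The case against.** A reader might infer that every patient whose status was ended by rescue within the hour counts as a success. The text does not support that. Ictal activity at T15 and any observed recurrence are failures, 6.3 describes unblinding and further treatment as following recurrence, and late cessation has its own secondary endpoint. A reader might also infer that the protocol counts death as success. It does not say so; it is silent.

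The remaining routes are narrow:
- **Before T15.** The infusion takes 10 minutes, the first response check is at T15, and 5.6 requires any earlier unblinding to be justified. Section 5.5.3 discourages certain drugs for 60 minutes. A second agent before T15 should be exceptional. Even so, the 5.5.3 list is short, is qualified by the investigator's judgement, and concerns valproate levels rather than endpoint scoring.
- **NCSE.** If the board reads the EEG as clear from T15, it had cleared before any drug given because of the T15 check. Scoring that initial cessation as response is blinded central reading working as intended. What remains is that the rest of the hour is read on a medicated EEG.

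The size is also open to challenge. The share m is an assumption applied to all true failures, most of whom cannot be converted. The planned 60% and 47% rest on studies that 8.4 says had differing time frames and endpoint definitions, so they are not shown to be rescue-free rates. With equal m the error is dilution, not a false claim of benefit.

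Finally, 8.5.2 leaves derived variables to the statistical analysis plan, which is not at hand. That is a fair answer for the event and censoring rules of time to cessation. It is weaker for the primary endpoint, because the protocol itself fixes what success and failure are.

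**Conclusion.** The point holds in limited form. Sections 8.2.1 and 8.1.1 do not make success conditional on the absence of other antiseizure or sedative treatment, or on survival, up to T60, and this conflicts with the stated aim of measuring the effect of VPA or LEV. The affected patients are those in the last four rows of the first table.

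Success rates would be overstated. The direction of bias in the comparison depends on whether such use is balanced between arms, and the documents do not tell. The power figures are illustrations under an assumed m, not estimates. The sample size of 454 is not wrong on this account. This should be fixed because it decides who counts as a primary success, but it does not by itself invalidate the comparison.

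**What to change.** This concerns scoring only; no clinical management changes.

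1. In 8.2.1 and 8.1.1, state that success requires no anticonvulsant, sedative or anaesthetic beyond the single allocated infusion from T0 to T60, and survival to T60. Otherwise the patient is scored as a failure, whatever the clinical or EEG-board reading.
2. Add a sensitivity analysis in which sedation given only for airway management or procedures is not a failure, so that a safety event is not silently turned into an efficacy failure.
3. In the time-to-cessation analysis, keep patients who meet rule 1's failure condition as not ceased to 60 minutes, rather than counting an event or censoring them at rescue.
4. Record drug and clock time for every such agent up to T60. The existing fields do not quite suffice. The emergency-medication item (7.1.3, 8.2.2) excludes the allocated drug, although 6.3 allows its repetition. The Visit 2 record of further antiepileptic treatment lists no clock time.

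The cost is a wording amendment, one small eCRF clarification and slightly lower reported success rates. The rule is best fixed before the analysis plan is written: 8.5.2 places that after 10% of patients' data are entered, when those patients' allocations will already have been opened at the sites.
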